#### Sample size

A sample size of 480 couples, 120 per each of the four study arms, was chosen to ensure sufficient statistical power to detect meaningful differences in our primary outcomes of couple-level ART/PrEP initiation and adherence between intervention and control groups. These power calculations assume 80% power, and an intraclass correlation coefficient (ICC) of 0.05 (based on the team’s previous R01 study with couples in Cape Town) [22], with an estimated follow-up of 95% at 3-month follow-up and 90% at 6-month follow-up. On average, a sample size of 97 community members in each of the 24 catchment areas was calculated to detect a 10% difference between control and intervention conditions on measures of stigma reduction. Using a two-sided chi-square test of proportions with a significance level of 0.05 and nested design model with additivity on the primary intervention effect (stigma awareness community workshop as compared with no community workshop) and secondary intervention effect (CHC+ as compared with HTS), our sample size was selected to ensure power for contrasts based on the presence of an interaction between the community-based stigma awareness workshop and the CHC+. For a hypothesis related to ART/PrEP initiation among couples in the CHC+ arm as compared with couples in the HTS arm, we will be able to detect a minimal effect size of 0.23. The minimal effect size of the CHC+ intervention on ART/PrEP adherence by couples in the CHC+ arm at 6 months is estimated to be 0.34 compared with couples in clinics in the HTS arm. For the evaluation of the efficacy of the stigma awareness workshop plus the CHC+ as compared with no stigma awareness workshop plus HTS (control), the minimal effect size related to ART/PrEP initiation is estimated to be 0.45. For examination of the intervention components’ effects (stigma awareness workshop and the CHC+) on ART/PrEP adherence), the minimal effect size is estimated to be between 0.26 and 0.6 for retention at 3-month and 6-month follow-up.

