#### Study research design

This study is a four-arm cluster randomized trial that has two interventions: a community stigma awareness workshop (for communities) and the CHC+ (for couples). Specifically, 24 Cape Town communities located near clinics that provide ART and PrEP were randomized into one of four arms (see **Fig 3**): (1) stigma awareness workshop (community) and HTS/PrEP/ART (couples); (2) stigma awareness workshop (community), and HTS/PrEP/ART with the CHC+ (couples); (3) no stigma awareness workshop (community) and HTS/PrEP/ART (couples; control); and (4) no stigma awareness workshop (community), and HTS/PrEP/ART with the CHC+ (couples). Twenty couples (a total of 480 couples), defined as young women and their primary male partners both aged 18 to 30 are recruited from each community. Depending on the study arm of their community, couples are provided with HTS/PrEP/ART and/or the CHC+. Couples are asked to return for two study follow-up appointments at 3- and 6-months post-enrollment. Communities are already assigned to receive either the stigma awareness workshop or no workshop, with baseline and repeated follow-up surveys with community members. Recruitment began in July 5, 2022 and is ongoing.

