#### Randomization

To achieve balance in allocation of population groups across the four study arms, stratified randomization by population group (Black African, Coloured, and Mixed) was conducted. A total of 24 catchment areas were selected from the list of 34 catchment areas. The sampling frame included 8 Black African, 8 Coloured and 8 Mixed communities. Within each of the 3 strata, the 8 areas were randomized to the four study arms in a 2:2:2:2 allocation.

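### The minimal effect sizes for the primary outcomes (0.23, 0.34, 0.45) cannot all be reproduced from the stated sample-size inputs on any one metric

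*Protocol article*

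**What the plan says.** All references are to the protocol article. The Sample size section gives the total as "A sample size of 480 couples, 120 per each of the four study arms" and says the calculations "assume 80% power, and an intraclass correlation coefficient (ICC) of 0.05". It adds follow-up of 95% at 3 months and 90% at 6 months, and a two-sided chi-square test of proportions at 0.05.

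It then lists the detectable effects. For initiation, CHC+ against HTS, "we will be able to detect a minimal effect size of 0.23". For 6-month adherence in the same comparison the figure is 0.34. For the workshop plus CHC+ against neither, "the minimal effect size related to ART/PrEP initiation is estimated to be 0.45". It does not say what kind of effect size these are, and it prints no control rates.

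On the design, the Study research design section says "24 Cape Town communities located near clinics that provide ART and PrEP were randomized into one of four arms", with 20 couples recruited per community. Under Randomization, within each of three strata "the 8 areas were randomized to the four study arms in a 2:2:2:2 allocation", which makes six communities per arm. The Statistical analysis plan and hypotheses section makes the couple the unit of analysis for initiation and adherence.

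**The concern.** This paragraph is the article's justification of 480 couples for the primary outcomes. It prints both the inputs and the outputs of a power calculation, so one can be checked against the other, and they do not agree.

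Two of the outputs, 0.23 and 0.45, concern the same outcome under the same assumptions. They differ only in how many communities are compared, yet they stand further apart than that difference allows. In addition, 0.23 is small enough to raise the question whether the ICC entered it at all.

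At stake is what a null result would mean. Someone who takes 0.23 as a standardised effect detectable with 80% power would think that such an effect had been excluded when it had not.

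**Working it through.** **Inputs.** There are 6 communities per arm. CHC+ against HTS, pooled over the workshop factor, is 12 v 12; the joint arm against control is 6 v 6. Each community has m = 20 couples, so 19 at 95% follow-up and 18 at 90%. The ICC is 0.05, taken as the correlation of couples within a community because the article does not name the level. With two-sided 0.05 and 80% power, the multiplier is 1.960 + 0.842 = 2.802, and its square is 7.849.

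**Formulas.** Design effect DE = 1 + (m − 1) × 0.05. Effective couples per group n_eff = communities × m / DE. Minimal standardised effect = 2.802 × √(2/n_eff). Power at effect d = Φ(d × √(n_eff/2) − 1.960).

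**Trying to reproduce the printed figures as standardised effects (h or d).**

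| Comparison | m | DE | n_eff per group | Minimal effect from inputs | Printed | Power at printed value |
|---|---|---|---|---|---|---|
| Initiation, 12 v 12 | 19 | 1.90 | 228/1.90 = 120 | 0.362 | 0.23 | 43% |
| Adherence, 12 v 12 | 18 | 1.85 | 216/1.85 = 116.8 | 0.367 | 0.34 | 74% |
| Initiation, 6 v 6 | 19 | 1.90 | 114/1.90 = 60 | 0.511 | 0.45 | 69% |

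The follow-up chosen for initiation hardly matters: full follow-up gives 0.357 and 0.505, and 90% gives 0.367 and 0.519. With t critical values on community degrees of freedom (20 for the pooled contrast, 10 for 6 v 6), the minimal effects are about 0.38, 0.39 and 0.57.

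**Was clustering applied to 0.23?** With no clustering and no loss, 240 couples per group give 2.802 × √(2/240) = 0.256. An effect of 0.23 needs 2 × 7.849 / 0.23² = 297 effective couples per group. Even unclustered, 240 give only 71% power. On this scale, then, 0.23 cannot come from the stated ICC and a two-sided test.

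**Cohen's w.** w = √(7.849 / total effective couples) gives √(7.849/240) = 0.18, √(7.849/233.5) = 0.18 and √(7.849/120) = 0.26. Power at the printed 0.23, 0.34 and 0.45 is then about 95%, above 99% and above 99%.

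**Risk difference.** No control rates are printed, so I assume 5% to 50%. The detectable difference is about 0.11 to 0.18 for 12 v 12 and 0.17 to 0.26 for 6 v 6. At the printed values, with 12 v 12 for the first two and 6 v 6 for the third, power is about 95% or more at 0.23 and above 99% at 0.34 and 0.45.

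**Ratio check.** The two initiation figures share every input except the number of communities. Halving that number multiplies any of d, h or w by √2 = 1.41. The printed ratio is 0.45/0.23 = 1.96.

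**One-sided variants.** These come near each figure, but only with different settings: 0.227 for 240 v 240 unclustered, 0.338 for 108 v 108 unclustered, and 0.448 for 120 v 120 with ICC 0.05. No one setting gives all three, and the article states a two-sided test.

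**The case against.** The strongest reply is that the metric is unnamed and that a chi-square test of proportions points to a risk difference or Cohen's w at least as naturally as to h. On those readings the printed pooled effects have more than 80% power, so no shortfall is shown. This stands, and it limits what can be concluded. It does not restore the figures, because values detected with 95% power or more are not minimal values at 80%.

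A second reply is that CHC+ against HTS may be an arm-to-arm contrast. The article sizes the sample for contrasts in the presence of an interaction and tests two arms at a time. As a 6 v 6 risk difference with an assumed 20% control rate and 20 couples per community, the detectable value is 0.233, which matches 0.23. But the joint-arm comparison for the same outcome is then also 6 v 6, where no control rate from 5% to 50% yields more than 0.26, so 0.45 is left unexplained. On the standardised scale the arm-to-arm reading lowers power at 0.23 to about 24%.

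Third, adherence may be analysed only among couples who start ART or PrEP. The article does not settle the denominator. The printed 0.34/0.23 = 1.48 therefore cannot be called impossible, although with all retained couples the ratio would be 0.367/0.362 = 1.01. I place no weight on that ratio.

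Fourth, a condensed article may leave metric and control rates to the full protocol. That is fair, and their absence alone would be no finding. The point here is that the printed outputs disagree with the printed inputs.

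A reader might also take the article's description of the model as nested for an error, since both interventions are assigned by community. It can simply mean couples within communities, and the article claims no within-community comparison of CHC+.

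**Conclusion.** The point holds in this form: 0.23, 0.34 and 0.45 cannot be derived together from the stated inputs on the standardised, Cohen's w or risk-difference scale, and 0.23 and 0.45 do not fit each other for the same outcome.

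The size depends on the metric. On the standardised scale the values should be about 0.36, 0.37 and 0.51. Power is then about 43% at 0.23, which is far from 80%, but about 74% at 0.34 and 69% at 0.45, which are moderate shortfalls. On w or risk difference, the pooled figures and the joint-arm 0.45 are larger than the design needs.

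A reader might infer that the trial is underpowered whatever was meant. The document does not support that, because the conclusion reverses with the metric. The calculations assume an ICC for couples within community, equal community sizes, a pooled 12 v 12 contrast for CHC+ and, for adherence, all retained couples. Control rates of 5% to 50% are my assumption and enter only the risk-difference reading.

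**What to change.** Recompute and restate the effect sizes in the Sample size section, including the 0.26 to 0.6 range given there, on one footing:

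- Name the metric and the assumed control rates.
- Say whether CHC+ against HTS is pooled (12 v 12) or arm-to-arm (6 v 6).
- Say whether adherence is analysed in all retained couples or only in those who initiate.
- Show the design effect 1 + (m − 1) × 0.05 and apply it to every figure.

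If the sponsor confirms the standardised scale with all retained couples, the values to print are about 0.36 (initiation) and 0.37 (adherence) for pooled CHC+ against HTS, and about 0.51 for the joint arm against control. With t critical values on community degrees of freedom they are about 0.38, 0.39 and 0.57. If another metric or denominator was meant, these numbers do not apply and the matching ones should be derived.

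The cost is a change of text. Enrolment and design stay as they are. On the standardised scale the stated detectable effects become less favourable.

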### Community

#### Community brief survey and workshop recruitment

Prior to conducting any brief community-level survey and workshop activities, trained outreach staff ensure that the study has been adequately introduced to key community leaders or gatekeepers, and that the necessary permission is granted to conduct these activities. During community mapping, they assist with identifying where to conduct assessments and the workshop, and addressing any security issues in the community. Trained outreach staff then identify areas where people congregate in the catchment area, including community malls, centres or halls, street corners, hair and beauty establishments where community members can be recruited for the brief community survey and workshop by distributing marketing flyers and describing the workshop objectives to community members.

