#### Data collection: Community

Baseline data on community stigma are obtained through the administration of a brief self-administered, paper-and-pencil questionnaire to individuals 18 or older residing in all 24 study communities surrounding the study clinics. The sample for the questionnaire is selected through convenience sampling. This questionnaire is a collection of validated stigma measures that have been modified for this study [33,34]. Individuals provide written consent prior to participation in the survey. We will conduct repeated surveys in all 24 communities 4 and 8 months later, through a repeated cross-sectional design to assess stigma awareness from the workshop (described below) and dissemination of information to community members who did not attend the workshop.

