#### Implementation of the community stigma awareness workshop

After the brief baseline survey has been completed, community stigma awareness workshops will be conducted in communities that were randomly assigned to receive this stigma awareness activity (N = 12). We expect on average to reach 100 community members to attend these workshops. These workshops can occur within a week of survey completion. The workshops take place in various community settings, such as community library workrooms, churches, sports halls, or temporary tented areas within the community with a minimum of 50 attendees, meaning one or two workshops will be conducted per community. The workshops are facilitated by the field team leads, field staff, and PAB members. Extensive awareness campaigns are conducted within the communities to inform residents about the upcoming workshop, through marketing materials and advertising the workshop with music and a loudspeaker and by word of mouth. These workshops take approximately 2 to 3 hours. Following the workshop, participants can complete a voluntary exit survey that will assess participant satisfaction and elicit suggestions and recommendations on the workshop delivery. The workshop participants are also provided with ART and PrEP information leaflets and resource guides for local services such as substance use rehabilitation centers and mental health services.

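### People are recruited for the stigma survey and the workshop in one step, although all 24 communities are surveyed and only 12 hold a workshop; survey recruitment should be separate and arm-neutral.

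*Protocol article*

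**What the plan says.** The section on community brief survey and workshop recruitment describes one activity with two purposes. Outreach staff find places where people gather, and people there are "recruited for the brief community survey and workshop by distributing marketing flyers and describing the workshop objectives". The section draws no distinction between workshop and non-workshop communities.

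Other sections fix the setting:

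- **Who is surveyed.** Under Data collection: Community, the baseline questionnaire goes to adults "residing in all 24 study communities surrounding the study clinics". It is self-administered on paper.
- **How they are chosen.** The same section states: "The sample for the questionnaire is selected through convenience sampling".
- **Later waves.** It also plans "repeated surveys in all 24 communities 4 and 8 months later, through a repeated cross-sectional design". Recruitment for these waves is not described separately.
- **Allocation.** Study research design states: "Communities are already assigned to receive either the stigma awareness workshop or no workshop".
- **Workshop.** The implementation section states: "After the brief baseline survey has been completed, community stigma awareness workshops will be conducted in communities that were randomly assigned". There are 12 such communities. On timing: "These workshops can occur within a week of survey completion".
- **Safeguards.** The eligibility section aims at a representative, gender-balanced sample and makes the survey anonymous. The screening section has staff introduce the study and explain the assessment before consent.

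**The concern.** In a convenience sample, the invitation decides who answers. An invitation built on a stigma workshop may draw people already sympathetic to its message. Telling people what the workshop aims to change, shortly before they report their own attitudes, can also signal the wanted answer. Because allocation is known when recruitment takes place, either mechanism can act in one arm more than the other.

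Aim 2 rests on this survey, and the Sample size section calls the workshop contrast the primary intervention effect. Randomising communities does not protect the contrast if respondents enter the sample differently by arm after allocation. The survey is anonymous and takes new cross-sections, so respondents cannot be linked across waves to remove such a shift.

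**Working it through.** **1. The sections side by side.** Survey: 24 communities. Workshop: 12. Recruitment: one joint step that includes the workshop objectives. The step can be carried out in two ways.

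- *Objectives described only where a workshop will be held.* The survey invitation then differs by arm, and self-selection and priming can differ with it.
- *Objectives described everywhere.* The invitation is then balanced. But respondents in both arms are primed, and 12 control communities hear part of the intervention message and are recruited for a workshop they will not get. This can dilute the contrast.

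The article does not say which applies. The stated safeguards do not settle it: neither says that recruitment is the same in both arms, or that it is kept apart from workshop promotion.

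**2. The survey's own figure.** The Sample size section gives 97 people per community on average, to detect a 10% difference (two-sided 5% test). It states 80% power and an ICC of 0.05, the latter from a couples study. No base rate is given, so 97 cannot be uniquely reproduced. With 12 communities per condition:

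- n per condition = 97 × 12 = 1164
- design effect = 1 + (97 − 1) × 0.05 = 5.8
- effective n = 1164 / 5.8 ≈ 201
- power: 80.3% for 20% v 10%, 63.9% for 30% v 20%, 52.1% for 50% v 40%

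The stated power is met at the first base rate only. The point here does not depend on this; the 10% target serves only as a yardstick.

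**3. Size of a bias, by assumption.** Let s be the share of respondents affected in one arm and d the shift in their reported stigma. Then bias = s × d. The article gives neither input. Assumed values:

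| s | d (points) | bias (points) |
|---|---|---|
| 25% | 5 | 1.25 |
| 50% | 10 | 5 |
| 75% | 15 | 11.25 |

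The middle row is half of the 10-point target, but only because of the values chosen.

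**4. Direction.** Take the 5-point case, assume that the description lowers reported stigma, and compare two possible analyses:

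| Objectives described in | Arms compared at follow-up | Change from baseline compared |
|---|---|---|
| workshop arm, baseline only | 0 | effect understated by 5 |
| workshop arm, follow-up only | overstated by 5 | overstated by 5 |
| workshop arm, every wave | overstated by 5 | 0 (cancels) |
| both arms, every wave | 0 from recruitment, but possible dilution | same |

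The sign depends on facts that the article does not give.

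**5. Effect on the test.** Assume a 50% control rate, no true effect, 1164 people per condition, arms compared at one wave, and clustering correctly allowed for. With p₁ = 0.50, p₂ = 0.50 − b and n the effective sample size:

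- SE = √[p₁(1 − p₁)/n + p₂(1 − p₂)/n]
- false-positive rate = Φ(−1.96 + b/SE) + Φ(−1.96 − b/SE)

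| artefact b | ICC 0 | ICC 0.02 | ICC 0.05 |
|---|---|---|---|
| 2 points | 16.2% | 8.7% | 6.9% |
| 3 points | 30.5% | 13.6% | 9.2% |
| 5 points | 67.7% | 29.3% | 17.1% |

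For b = 5 points and ICC 0.05: SE = √(0.4975/200.7) = 0.0498, b/SE = 1.00, rate 17.1%. A larger sample makes this worse, because the bias stays while the standard error shrinks.

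**The case against.** The strongest reply is that one compressed sentence is being read too literally. The section covers two activities under one heading, and describing the workshop objectives may belong only to the workshop half. The screening section has its own survey introduction, about the study and the assessment, with no distinction by arm. The workshop has its own promotion and follows completion of the baseline survey. Exact scripts belong in the manualized field procedures, which are not shown.

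Part of this stands. The field manual may keep the two activities apart, and the sentence can be read that way. But the published text states a joint procedure. The survey introduction does not undo it, since it follows recruitment and does not say that the workshop goes unmentioned. Holding the workshop after the survey does not mean promoting it after the survey.

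The reply also rightly blocks several stronger inferences that a reader might draw:

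- *Control communities cannot be approached in this way.* The article does not say what they are told.
- *The invitation changes between waves.* Recruitment at 4 and 8 months is not described.
- *A baseline-adjusted contrast is biased, so the effect is understated.* No such Aim 2 analysis is stated. The sizing refers to a chi-square test of proportions, and the modelling text is written mainly around couple outcomes.
- *The workshop always follows within a week.* The article says only that it can.

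A missing attendance question, or missing age and sex adjustment, cannot be claimed either, because the questionnaire and the Aim 2 model are not shown. Finding workshop attendees, or people they have informed, in the follow-up samples is intended and is not part of this bias.

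**Conclusion.** The point holds as a fault in a stated procedure. Recruiting for outcome measurement and for the intervention in one step, with the workshop objectives as part of the approach, either ties survey recruitment to arm or primes both arms and carries part of the message into control communities. Either way the recruitment text needs to be reconciled with a survey in 24 communities and a workshop in 12.

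The article does not show that a bias has occurred, and neither its direction nor its size can be derived. The 5-point figure rests wholly on an assumed 50% share and an assumed 10-point shift, and the false-positive rates on an assumed 50% control rate. They show that a moderate recruitment artefact would matter against a 10% target, and no more. The change is worth making because it is cheap and closes both routes.

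**What to change.** In the section on community brief survey and workshop recruitment, separate the two activities:

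- Use one arm-neutral survey script, flyer and venue procedure in all 24 communities at baseline, 4 months and 8 months, without describing the workshop objectives.
- In the 12 workshop communities, promote the workshop only after the questionnaire is handed in.
- State what has been said so far in non-workshop communities and at any follow-up wave already run.

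If the field manual already does this, correcting the published text is enough.

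The cost is a reworded script and flyer, and a separate recruitment step for the workshop. No sample size changes. Communities already surveyed at baseline under the joint approach need a sensitivity analysis, such as a comparison of arms at follow-up without the baseline wave. That comparison is free of the problem only if the follow-up waves were recruited neutrally.
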